## Abstract

**Background:**

Nursing home residents’ health and psychosocial well-being may be influenced by their often-sedentary lifestyles, which arise due to physical barriers like steps, an unwelcoming environment, limited awareness of the importance of physical activity (PA), and a lack of orientation. While exercise interventions are important for maintaining or improving physical and cognitive functions, they may not help increase daily PA behavior. Therefore, the PROGRESS study aims to investigate the short- and long-term effectiveness of tailored and combined physical exercise and environmental interventions for improving PA behavior and physical functioning among nursing home residents.

**Methods:**

The study employs a cluster-randomized controlled crossover design with four intervention groups. Participants will be randomly assigned to one of four groups: a combined exercise and guided environmental intervention (physical activity-promoting culture), an exercise intervention, a guided environmental intervention, or a non-guided environmental intervention. The exercise intervention involves group-based sessions twice a week, while the environmental intervention focuses on implementing PA into daily routines. The guided environmental intervention is equivalent to the non-guided one but provides additional support two to four times weekly. We aim to recruit at least 120 participants from six nursing homes. Each facility will receive two interventions in a 16-week crossover design (36 weeks in total, including weeks for measurements), followed by a 16-week non-guided environmental intervention (follow-up phase). Primary outcomes include steps per day as an indicator of PA behavior, and the Short Physical Performance Battery (SPPB) to assess physical functioning.

**Discussion:**

We hypothesize that the physical activity-promoting culture will yield superior effects than either intervention alone on the primary outcomes. Furthermore, both the guided environmental intervention and the exercise intervention are expected to be more effective than the non-guided environmental intervention. We aim to encourage nursing home residents to actively participate in social life and to derive guidelines for health promotion.

**Trial registration:**

The study is registered at the German Clinical Trial Register (DRKS) under registration number de DRKS00031020 (23.02.2023) and has received ethical approval from the University of Münster, Faculty of Psychology and Sports Science (2022-40-CVR).

## Introduction

The aging process is associated with a decline in physical and cognitive abilities as well as a higher incidence of adverse health events. Therefore, the older population tends to have more problems with activities of daily living (ADL) and impaired psychosocial well-being (Guralnik et al., 1993). Demographic changes mean that the average age of the population is increasing, leading to a greater number of highly aged individuals who will require support and care. The number of people in Germany who require care is currently around 4.1 million, and this care is provided for both outpatient (home care) and stationary (nursing home) settings (de Jong et al., 2023). Due to physical and cognitive impairments, most nursing home residents require assistance in their daily lives, and some even experience severe loss of independence, necessitating intensive care (Stockel et al., 2017; Bischoff et al., 2023). Therefore, it is crucial to promote health among older adults who need care, particularly those with multiple health conditions (Araujo de Carvalho et al., 2017).

The decline in physical and cognitive abilities and the increase of adverse health events tend to happen alongside sedentary behavior and a less active lifestyle (Provencher et al., 2008), therewith inducing a vicious cycle. Sedentary behavior reduces physical and cognitive functioning not only due to less cognitive and physical stimulation but also because of fewer social interactions (Schrempft et al., 2019; Giurgiu et al., 2020). Age-related cognitive decline affects almost all dimensions of cognition, including spatial cognitive abilities like spatial orientation and navigation (Moffat et al., 2001). This, in turn, can hinder an active lifestyle, especially one’s mobility within a nursing home and its environment (life space mobility, LSM).

Physical and cognitive abilities as well as psychosocial well-being can be maintained or improved even in older adults suffering from multiple health problems by appropriate interventions such as physical exercise (Mulrow et al., 1994; Kryger and Andersen, 2007; Pedersen and Saltin, 2015; Cordes et al., 2021a). However, the type, design, and duration of the training must be considered to achieve training effects. For example, interventions that combine cognitive and physical exercise components tend to more strongly benefit both motor and cognitive performance than interventions focused on pure motor or cognitive training (Wollesen and Voelcker-Rehage, 2014). Combined physical and cognitive training interventions have been shown to improve physical abilities, including physical strength, cardiorespiratory fitness, flexibility, balance, and everyday functionality and mobility (Fiatarone et al., 1990; Sherrington et al., 2008; Liu and Latham, 2009; Marmeleira et al., 2009; Gine-Garriga et al., 2010; Matsuda et al., 2010; Steib et al., 2010). Furthermore, these interventions have been demonstrated to reduce falls and physical frailty. They also seem to benefit cognitive functions (Marmeleira et al., 2009), including visual attention, executive functioning, and speed of information processing. With respect to the design, duration, and frequency, intervention studies that adapt to individuals’ abilities, focus on personal resources and are conducted twice a week for 45–60 min have been found to have the most positive effects (Wollesen and Voelcker-Rehage, 2014; Cordes et al., 2021a).

Beyond exercise interventions, promoting daily physical activity (PA) in nursing homes seems to be an urgent issue, as nursing home residents do not get sufficient PA in their normal lives. For example, Auerswald et al. (2022) investigated the PA behavior of nursing home residents using activity trackers (Fitbit Zip). On average, nursing home residents took 1.020 steps per week (–600 m) and spent 9 h per day sitting or lying down. At least two and a half of these hours were spent sitting or lying down continuously (see (Clark and Sugiyama, 2015; Vallance et al., 2018) for similar results). These findings indicate that the daily lives of nursing home residents lack PA, which can harm their health. Research has shown that there is a correlation between the amount of time spent sitting and the risk of mortality (Ebeling et al., 2013; Ministry of Health, 2013).

Only a few approaches have aimed to improve daily PA behavior. Integrated into a classic group training program, Wollesen et al. developed a training concept for care facilities in which both physical skills and spatial orientation are practiced (Wollesen et al., 2020a). Programs developed within long-term care institutions have demonstrated that individualized exercise regimens can be both safe and effective, even when integrated into routine care practices (Braun et al., 2015; Cordes et al., 2021b), virtual cycling systems (D'Cunha et al., 2021), and virtual reality training (Scheicher et al., 2017) to encourage movement and increase engagement. Second, physical space modifications include dynamic lighting (Baandrup and Jennum, 2021) or enriched gardens (Bourdon and Belmin, 2021). Thirdly, group activity spaces used giant exercise board games (Mouton et al., 2017), outdoor exercise parks with age-friendly stations (Levinger et al., 2023), or indoor exercise stations (Fleiner et al., 2015; van Delft et al., 2020). Specifically, Fleiner and colleagues (2015) set up an “active corridor” in different wards of a geriatric psychiatric clinic, with posters instructing patients on how to exercise. Patients were asked to walk in the active corridor for 20 min, four times a day, three times a week. In a different study, Van Delfts’s group used a step-by-step method (Grol and Wensing, 2015) to develop an “action plan” for four wards of a hospital in Uetrecht. The plan was developed and implemented with the involvement of patients, physiotherapists, nurses, doctors, and patients’ relatives (van Delft et al., 2020). This included the creation of exercise guides and material, as well as 7-min workout videos for lying, sitting, and standing, and QR-code walking routes throughout the building. The reported performance measures showed improvements in physical activity as well as physical function in most cases. For example, group activity spaces recorded gains in mobility, balance, and strength (Scheicher et al., 2017; Buckinx et al., 2020; Bourdon and Belmin, 2021; Mak et al., 2022). Incorporating such environmental interventions within a nursing home could increase PA behavior and promote social contact, as well as improve spatial orientation and LSM.

So far, studies have focused on either group-based physical exercise interventions or environmental interventions. While both intervention models show positive results, exercise interventions primarily promote physical functioning, whereas environmental interventions positively affect physical activity. Therefore, we suggest combining group-based physical exercise interventions with approaches to explicitly increase PA levels. As such, we developed this protocol to offer a new intervention model, namely, a physical activity-promoting culture, which combines both types of interventions: group-based physical exercise classes and environmental interventions. We hypothesize that the physical activity-promoting culture might lead to larger effects on PA behavior and physical functioning in nursing home residents than each intervention alone. Additionally, we expect that, individually, the guided environmental intervention and the exercise intervention will be more effective than the non-guided environmental intervention. Thus, the overall aim of the PROGRESS study is to encourage active participation in social life among nursing home residents and to develop guidelines for health promotion.

## Methods

The SPIRIT statement was used as a guideline for this protocol paper (Chan et al., 2013) (see Supplementary Table S1).

### Trial design

Based on existing research and the physical exercise recommendations mentioned above, this monocentric intervention study is conducted through a controlled cluster-randomized crossover design with four arms. The four interventions are randomly paired and ordered using MATLAB (‘nchoosek’ and ‘randperm’ functions), ensuring that each intervention will be combined with each of the other three interventions once. These six different intervention combinations were then clustered randomized to the nursing homes in the agreed order. In general, the trial design can be divided into an intervention and a follow-up phase with four separate weeks of measurements (t1-t4). So t1 is the baseline measurement time point, t2, with a double role, corresponds to the post-measurement point for the first intervention as well as the pre-measurement point for the second intervention phase. According to this, t3 will be the post-measurement point for the second intervention. 16 weeks after t3, the study will be concluded with the follow-up measurements (t4) after 52 weeks (see Figure 1). The date of first enrollment was August 2022.

**FIGURE 1 F1:**
[figure not shown]
Study design- CONSORT Flow-Diagram of the PROGRESS project. Note: The power calculation determined that a total of 116 participants were required. To improve traceability, this number has been rounded up to 120.

### Participants

#### Ethics approval and trial registration

The study is being conducted according to the Declaration of Helsinki and the guidelines of Good Clinical Practice (GCP). All participants will give written informed consent before enrollment and are allowed to leave the study at any time without any consequences. The ethics committee of the Faculty of Psychology and Sports Science of the University of Münster, Germany, has approved the study protocol (2022-40-CVR). The study was registered at DRKS. de with registration number DRKS00031020 on 23.02.2023.

#### Recruitment of nursing homes

The study has aimed to identify at least six nursing homes around Münster, Germany, that are willing to take part. To ensure enough participants, institutions were selected based on their number of residents (ideally >100), as we aimed to recruit 10–20 participants per nursing home (n = 116) and 29 per intervention arm (see power calculation). The first point of contact was with the nursing home management via email or telephone. During this initial contact, the possibility of participating in a study to promote physical activity was enquired about, without providing any details. Participation is voluntary and not remunerated. Nursing home recruitment ended in the third quarter of 2023.

#### Recruitment of participants

Once a nursing home expresses interest in participating, a standardized information event will be held to introduce the PROGRESS project to all interested residents, staff, and relatives of residents. The information event will also serve as a needs assessment, as initial ideas for promoting a more active lifestyle will be collected. After the event, a nursing home employee will be asked to list all residents who meet the inclusion criteria and are interested in participating. Each nursing home resident on the list will be informed about the project and the conditions of participation in a standardized one-on-one meeting conducted by a research assistant. This meeting will follow the structure of the agreement paper, and it will be checked whether the participants are cognitively able to follow the conversation. Any outstanding issues will be clarified, and if the participant fits the eligibility criteria, consent to participate will be obtained. If a nursing home resident is unable to sign documents, the consent meeting will be conducted with the legal guardian. Participants will be blinded; they will not be aware of interventions in other nursing homes, and they will not be in contact with residents from other nursing homes.

#### Eligibility criteria

Inclusion criteria are: (i) voluntary participation, (ii) ability to participate in group training, (iii) minimum age of 60 years, (iv) ability to understand and implement instructions given by a trainer, and (v) ability to sit freely in a (wheel)chair. No other criteria are applied. If a study participant no longer fulfills the inclusion criteria due to a natural, age-related deterioration in general condition, they will be excluded from study participation (but they will be welcome to continue participating in the interventions voluntarily).

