### Statistical analysis

The descriptive statistics will be presented as either group mean values and standard deviations/errors or medians and interquartile ranges, depending on the distribution of the outcome measures. The intervention effect for the primary outcomes (Number of Steps and SPPB) will be analyzed separately using a 4 (between group: PA-promoting culture intervention, guided environmental intervention, non-guided environmental intervention, or exercise intervention) × 2 (within test time point: t1:t2, and t2:t3) linear mixed model, where participants can be nested within nursing homes and be calculated as a random effect. The Follow-Up effects will be analyzed additionally using a 4 (between group: all interventions) x 3 (within test timepoint: t1/t2 – t2/t3 – t4). If baseline differences are found, the baseline assessment values, as well as age and sex discrepancies, will be included as covariates in the statistical model. In cases of statistically significant interaction effects, Bonferroni-adjusted *post hoc* tests (such as t-tests or Wilcoxon tests) will be employed to identify significant differences between groups from baseline to post-allocation testing. The data will be pre-processed and analysed using SPSS.

The effect size will be determined using Cohen’s f, which indicates the magnitude of treatment effectiveness and helps assess whether a statistically significant difference is practically significant (Cohen and Ebl, 1988). Cohen’s f values are classified as small (0 ≤ f ≤ 0.24), medium (0.25 ≤ f ≤ 0.39), or large (f ≥ 0.40) (Grissom and Kim, 2011). For *post hoc* analysis, Cohen’s d effect size will be calculated. Additionally, PSdep scores (probability of superiority for dependent samples) will be calculated as an estimate of effect size in non-parametric *post hoc* tests. The significance level will be set at p < 0.05. An intention-to-treat analysis will be conducted, considering all participants in the groups to which they were randomly assigned, regardless of whether they received or adhered to the assigned intervention. We will control participation in the interventions to analyze the effect of the intervention in more detail. Multiple imputations will be used to handle missing data, assuming that the missingness is random. If more than 40% of participants are lost to outcome assessment or demonstrate insufficient participation in training sessions, an additional per-protocol analysis will be conducted.

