### Sample size estimate/power calculations

Statistical power analysis was conducted to estimate the sample size to test our hypothesis in G*Power (Version 3.1.9.4, Heinrich Heine University of Duesseldorf) (Faul et al., 2009). The following input parameters were used to obtain small-sized test × group interaction effects within an ANOVA: effect size (*f* = 0.15) (i.e., a small effect, (Tudor-Locke et al., 2011), type I error (α = 0.025), type II error (1-β = 0.8), number of groups (n = 4), number of measurements (n = 2), correlation between measurements (r = 0.60).

The size of the estimated sample to generate sufficient power to achieve the small effect is N = 88. To compensate for the estimated dropout rate of 30% (e.g., 20% lost to follow-up; plus 10% mortality) we plan to include a total of N = 116 participants. Based on the study design, we will integrate N = 29 participants in each condition.

Regarding the special cohort, recruiting approximately 30 participants per intervention arm per nursing home seems unrealistic, so multiple nursing homes will be needed for each intervention arm. As the number of nursing homes is also limited, each one needs to take on more than one intervention arm to reach a total of ∼30 participants. By the life expectancy of the special cohort and for ethical reasons, we have limited the maximum study duration to 1 year per participant. This means that each participant can complete two intervention phases and one follow-up phase per year, nested in a nursing home. In terms of the four intervention arms, this means six different possible combinations (this means six different nursing homes), each with 10–20 nursing home residents participating in the study.

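### Residents who deteriorate are excluded from the study after allocation, which either breaks the intention-to-treat analysis or leaves decline-related gaps to be imputed as missing at random

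*Protocol article*

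**What the plan says.** All of this is in the protocol article; no separate analysis plan is at hand.

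- **Eligibility criteria.** Apart from voluntary participation and age, the criteria are the ability to join group training, to follow a trainer's instructions, and to sit unaided in a chair or wheelchair. A participant who "no longer fulfills the inclusion criteria due to a natural, age-related deterioration in general condition" is taken out, yet may keep attending the sessions: "they will be excluded from study participation (but they will be welcome to continue participating in the interventions voluntarily".
- **Outcome measures, Table 1.** Eligibility screening and allocation come before the baseline assessment t1, so an exclusion during the study falls after allocation.
- **Statistical analysis.** The intention-to-treat analysis is described as "considering all participants in the groups to which they were randomly assigned, regardless of whether they received or adhered to the assigned intervention". For gaps, "Multiple imputations will be used to handle missing data, assuming that the missingness is random". The only further analysis named for losses is per-protocol, under the condition "If more than 40% of participants are lost to outcome assessment or demonstrate insufficient participation in training sessions".
- **Sample size estimate/power calculations.** The plan allows for an "estimated dropout rate of 30% (e.g., 20% lost to follow-up; plus 10% mortality", with N = 116 enrolled.
- **Primary outcomes.** SPPB runs from 0 to 12 and each component starts at 0. For steps, a day with fewer than 6 hours containing a step, or failing the three-a-day criterion, counts as a non-wearing day and is dropped.

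**The concern.** The trigger for exclusion is not administrative. Two of the three abilities are physical, and losing them is closely related to what SPPB and daily steps measure. An unfavourable course can therefore end a resident's outcome data, even for someone still living in the home and still attending the sessions.

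At stake is whether the analysis compares the groups as allocated. If arms differ in how many residents decline to the point of exclusion, the residents left in each arm are no longer comparable, and the imputation assumption does not repair this because the reason for the gap is the unobserved decline itself. The crossover adds to it. Under Trial design, t2 closes the first phase and opens the second, so a resident excluded in the first phase also contributes nothing observed to the home's second intervention.

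**Working it through.** **1. The two possible meanings of the exclusion sentence.**

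| Meaning of excluded | Set against the intention-to-treat statement | Consequence |
|---|---|---|
| Out of the analysis | Direct contradiction: not all participants are analysed as assigned | Selection on a post-allocation event related to outcome |
| Out of assessment, kept in the analysis by imputation | Consistent in form | Validity rests on missing at random, although the values are missing because of decline |

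The text does not say which is meant. Neither is satisfactory.

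**2. How many residents could be affected.** The plan's own inflation is 88 × 1.30 = 114.4, and the next multiple of four is 116. (Whether 88 itself is right is a separate matter and has no bearing here.) Applying the stated allowances to 116:

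- total loss: 0.30 × 116 = 34.8, about 35
- mortality: 0.10 × 116 = 11.6, about 12
- loss to follow-up from any cause: 0.20 × 116 = 23.2, about 23

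Deterioration exclusions are some unstated part of the 23, so the range is 0 to about 23.

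**3. What missing-at-random imputation does when the lowest values are the missing ones.** This is an illustration under assumptions that are not in the document. Outcomes are in SD units, y = 0.6·b + 0.8·e, with b the baseline and 0.6 the correlation (the value in the power calculation; √(1 − 0.6²) = 0.8). The lowest outcomes are lost, and each lost value is imputed by regression on baseline among the retained residents of the same arm. There are 1,000,000 simulated residents per arm.

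| Lowest share lost | Arm mean overstated by |
|---|---|
| 10% | 0.14 SD |
| 20% | 0.26 SD |
| 30% | 0.39 SD |

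**4. What this does to the contrast between two arms.**

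- Equal loss of 30% in both arms, true effect 0.30 SD: estimated 0.30 SD, so practically no bias.
- Unequal loss, 30% in the comparator and 20% in the treated arm, true effect 0: estimated −0.12 SD.
- One common deterioration threshold in both arms, true effect 0.30 SD:

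| Lost, comparator | Lost, treated | Estimated effect |
|---|---|---|
| 10% | 6% | 0.24 SD |
| 20% | 13% | 0.21 SD |
| 30% | 21% | 0.18 SD |

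If an effective arm prevents decline, the estimate therefore moves towards the null. If arms lose residents for other reasons, the direction is open.

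**5. Whether any named analysis would catch this.** The per-protocol trigger is 40%, above the planned 30%, and a per-protocol set would select further on the same residents. It is no check on the missing-data assumption.

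**The case against.** The strongest reply is that the sentence speaks of study participation, not of analysis. Read that way, excluded residents stay in the analysis set through imputation and the sections fit together. That stands. A reader might infer a flat contradiction with intention-to-treat, but the text supports this on only one of the two meanings.

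A reader might also infer that the worst outcomes are systematically removed. The document does not support that in full. The physical floor is low: a wheelchair user who scores 0 on every SPPB component can remain eligible if still able to join the group and follow instructions. The third ability is cognitive, so some exclusions need not reflect physical decline. Much SPPB decline therefore remains observed, and an imputation that uses a resident's own earlier values would carry some information.

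A third tempting inference is that the plan gives SPPB and step values to residents who have died. The article never says so. It follows only from a general imputation rule without an exception, together with mortality being counted as dropout in the sample size. The full protocol or analysis plan may treat deaths separately, and details such as the variables in the imputation model are properly left there.

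Finally, the primary test is a group-by-time comparison, so optimistic arm means matter less than differential loss. The loss allowance also appears to cover the whole study of up to a year, whereas each main contrast spans one 16-week phase, so loss per contrast is probably smaller. Both points limit the size. They do not remove the problem, because the exclusion is a stated rule and not an omission, and following it stops collection of data that could often still be obtained.

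**Conclusion.** The point holds in a limited form. As written, the plan stops outcome collection after allocation because of decline related to the primary outcomes. It then either drops those residents, against its intention-to-treat statement, or relies on a missing-at-random assumption that is not plausible for them. Under the second meaning, post-baseline arm means would be too favourable. The between-arm contrast is biased if exclusion differs between arms, towards the null if an effective arm prevents decline, and is close to unbiased if exclusion is equal.

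The size cannot be determined from the document. The number of deterioration exclusions lies anywhere from 0 to about 23 of 116, and the SD shifts shown above rest on assumed loss patterns. A reader might want to express the bias in SPPB points against the 1.0 to 1.3 points called clinically meaningful. That would need the true gap between excluded residents and their imputed values, and the difference in exclusion between arms, and the document gives neither.

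**What to change.** Reconcile the Eligibility criteria and Statistical analysis sections:

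- Replace the exclusion sentence. Residents who no longer meet the criteria stay in outcome assessment at the remaining time points, and in the analysis as assigned, unless consent is withdrawn.
- Score SPPB components that cannot be performed for physical reasons as 0, which the scale allows. A component not done because instructions are no longer understood should not be scored 0 on that ground.
- For outcomes still missing through deterioration, add a missing-not-at-random sensitivity analysis with a delta adjustment. This must include steps, because a resident who hardly walks will often fail the wear rule and yield no valid days even if follow-up continues.
- State that values after death are not imputed under the missing-at-random rule.

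The cost is a few extra assessments of residents, some of whom may still be attending sessions, plus one sensitivity analysis and the wording. First enrolment was in August 2022 and recruitment of homes ended in the third quarter of 2023, so some assessments may already be past; for those, only the analysis changes apply.
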